### Study duration

The study period is defined as being 12 weeks on a particular course of treatment. Where patients continue treatment beyond 12 weeks, those being treated at home can continue to do so. However, if they prefer to be treated in hospital they can transfer. Those patients randomised to hospital treatment cannot cross over to treatment in the community, since community-based treatment is not standard practice locally. Patients stopping treatment earlier than 12 weeks are not replaced in the study, but the reason for stopping is noted. They are included for the collection of study outcomes at 12 weeks, since analysis is on an intention-to-treat basis.

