### Study interventions

The Investigator has primary responsibility for the welfare of the patient for the duration of the study, whether receiving treatment in hospital, at home or in the GP surgery. Patient treatment is governed by a single set of standard operating procedures in use at CUH, WSH (and the GP surgeries involved in this study.

The Investigator is responsible for prescribing all treatment for trial patients, but can delegate this task to a member of his or her junior staff, as is standard clinical practice.

The treatment study period for this trial is 12 weeks, since most treatments are expected to be prescribed for at least this period of time. All planned treatment for a study patient will be delivered in the location to which the patient is randomised. Treatment of patients within the community may be aborted and transferred to hospital in the event of significant problematic drug-related toxicities, occurrence of a serious adverse event (SAE), on request by the patient, or following discussion between the community chemotherapy nurse and the Investigator who may feel it is in the patient's best interest to do so. The Investigator will review the patient in clinic prior to study entry and on completion of the study (whether at 12 weeks, or sooner in the case of early withdrawal). For patients continuing treatment beyond 12 weeks, the Investigator will review the patient on completion of the planned treatment or at 24 weeks, whichever is sooner.

All anticancer treatment and other prescribed drugs are dispensed by the oncology pharmacists in the respective hospitals, according to local policies. On the designated day, prescribed drugs for patients receiving treatment in the community are dispensed and placed with a copy of the patient prescription sheet in a designated box, ready for collection by the community chemotherapy nurse from the oncology pharmacy at a previously arranged time. The prescription sheet copy is returned to the oncology pharmacy within 48 hours of treatment.

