###### iv) *Patient safety*

CUH and WSH have in place a comprehensive set of policies and procedures governing community-based care. Specifically for cancer, the Cancer Treatment in the Community (CTC) policy identifies low risk patients and low risk treatments usually offered to patients in the hospital out-patient and day unit facilities which are potentially suitable for delivery in the community (Table 1). In addition, the CTC policy describes a clinical governance framework for ensuring patient safety in the community, reflecting standard policies and procedures adhered to when delivering cancer treatment in hospital. To be considered for this trial, both the patients and the treatment being offered are required to meet the criteria listed in the CTC Policy.

The treatments given to patients taking part in this trial are by definition those which are well established, with an excellent safety record. Our hypothesis is that patients would not be adversely affected or harmed by receiving treatment in the community. Appropriate safety measures and procedures are in place for community treatment, to provide a safe environment considered to be equivalent to the hospital setting.

Patient safety will be evaluated by recording the number of adverse and serious adverse events which occur during the study period (see safety procedures).

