### Safety procedures

#### Adverse events

For the purposes of this trial, an adverse event (AE) is defined as:

- any unscheduled contact (e.g. phone calls, face-face visits etc) made by the patient, or carer to the outpatient or community treatment nurse, Investigator or member of his/her team, GP, or other support staff in relation to their current course of treatment.

- any unscheduled contact (e.g. phone calls, face-face visits etc) made by the out-patient, or community treatment nurse to the Investigator or member of his/her team, GP, or other support staff relating to the management of the patient receiving treatment.

To ensure accurate collection of trial-specific AEs, trial patients and treatment delivery nurses are issued with a purpose-designed diary in which to record all occasions when unscheduled contact is made. Specific information regarding contact is also requested. All AEs which occur from randomisation until the final trial visit are recorded. Specific information to be recorded in the diary regarding AEs includes the date and time of occurrence, main reason for making contact, with whom contact is made and outcome.

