#### Serious adverse events

For the purposes of this trial, a serious adverse event (SAE) was defined as including any event which:

- results in death, regardless of cause.

- is life-threatening (immediate risk of death).

- requires hospitalisation or prolongation of existing hospitalisation, excluding those planned for cancer treatment, disease related procedures, or placement of an indwelling catheter, unless associated with other serious events.

- results in persistent or significant disability/incapacity.

- consists of a congenital abnormality of birth defect.

- involves grade 3 or 4 (severe or life threatening) drug-related toxicities.

- results in the patient's treatment being switched from the community to hospital-based treatment.

This trial is not evaluating treatment *per se*, but the venue of treatment delivery. Thus, reporting of drug-related AEs is limited to reporting of severe or life threatening toxicities, according to National Cancer Institute, Common Toxicity Criteria.

All SAEs which occur from randomisation until the final trial visit are recorded. All SAEs are reported to the CCTC immediately, by completing an SAE form, and assessed by the Chief Investigator. Autopsy data, where available, for deaths occurring from randomisation until 28 days after the last planned treatment administration are provided to the CCTC.

The relationship of SAEs to treatment delivery venue is assessed using the following definitions:

- Not related - The adverse event would definitely have occurred whatever the venue

- Unlikely to be related - The adverse event would probably have occurred whatever the venue

- Possibly related - The adverse event had a timely relationship to treatment venue. However, a potential alternative aetiology existed.

- Probably related - The adverse event had a timely relationship to treatment venue and a potential alternative aetiology was not apparent.

- Definitely related - The adverse event had a timely relationship to treatment venue and a potential alternative aetiology was not apparent. Upon switching treatment to hospital-based delivery, the adverse event would definitely not occur.

'Unlikely' and 'Not related' are considered not treatment venue related. 'Definitely', 'Probably' and 'Possibly' are considered treatment venue related.

In the case of an SAE, the subject will be followed up until recovery or stabilisation. The Investigator will take all measures necessary to resolve any SAE.

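### SAE recording ends at a final trial visit that may come before week 12 and does not match the 28-day autopsy rule, so late serious events can go unrecorded

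*Protocol article*

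**What the plan says.** All references are to the protocol article.

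- **Serious adverse events.** Death from any cause is an SAE. On the recording window: "All SAEs which occur from randomisation until the final trial visit are recorded". The Adverse events section uses the same end: "All AEs which occur from randomisation until the final trial visit are recorded".
- **Serious adverse events, autopsy rule.** "Autopsy data, where available, for deaths occurring from randomisation until 28 days after the last planned treatment administration are provided to the CCTC".
- **Study interventions.** The investigator reviews the patient "on completion of the study (whether at 12 weeks, or sooner in the case of early withdrawal"). Patients treated for longer are seen again when planned treatment ends or at 24 weeks, whichever is sooner. Recording and collection of data and Table 1 make that later data point optional.
- **Recording and collection of data.** A move from community to hospital counts both as an SAE and as withdrawal from the trial. Hospital-arm patients cannot move the other way.
- **Study duration.** "The study period is defined as being 12 weeks on a particular course of treatment". Patients who stop treatment early stay in for outcome collection at 12 weeks, on intention-to-treat grounds.
- **Patient safety.** "Patient safety will be evaluated by recording the number of adverse and serious adverse events which occur during the study period".

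**The concern.** Three end points for serious harm stand side by side: the final trial visit, the end of the 12-week study period, and 28 days after the last planned dose. The first is the one that governs SAE recording, and it is the least stable, because it moves with withdrawal and with an optional visit.

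The number of AEs and SAEs is the trial's only stated measure of patient safety, and the accompanying hypothesis is that community patients are not harmed. If recording closes early, serious events that surface late are missing from that count. A death could reach the trials centre through an autopsy report and still not be a recorded SAE. Early closure by transfer can happen only in the home and GP surgery arms, so the loss need not be equal across arms.

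**Working it through.** The plan gives no figure that depends on this window, so there is none to reproduce. The check compares the passages and then sizes the gap.

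**1. Which end date applies to whom**

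| Patient | Closing review, as written | Competing statement |
|---|---|---|
| Completes 12 weeks, then stops | Week 12 | Autopsy rule: last planned dose + 28 days |
| Stops treatment early | Sooner than week 12 if treated as withdrawal (Study interventions) | Kept to 12 weeks (Study duration) |
| Transfers from community to hospital | Withdrawal (Recording and collection of data), so possibly sooner | Events counted over the 12-week study period (Patient safety) |
| Continues past 12 weeks | Week 12, or the optional point at end of treatment or 24 weeks | Events counted over the 12-week study period (Patient safety) |

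**2. Size of the gap after the last dose**

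Input from the document: the 28 days in the autopsy rule. Assumption: g, the days from last dose to final visit, which the document does not give. The last planned dose is taken to be the last dose given.

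Uncovered days = max(0, 28 − g); uncovered share = uncovered days / 28.

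| g (days) | Uncovered days | Share of 28 |
|---|---|---|
| 0 | 28 | 100% |
| 7 | 21 | 75% |
| 14 | 14 | 50% |
| 21 | 7 | 25% |
| 28 or more | 0 | 0% |

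These are days without recording, not numbers of events missed. The document gives no event rates from which to estimate the latter.

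**3. The same early stopper under the two readings**

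Assume a last dose on day 42 and count week 12 as day 84.

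- Followed to week 12 (Study duration): g = 84 − 42 = 42, so max(0, 28 − 42) = 0 uncovered days.
- Final review at stopping (Study interventions, if stopping is treated as withdrawal): g = 0, so all 28 days are uncovered. In addition, 84 − 42 = 42 days of the study period itself lie outside SAE recording.

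The result depends entirely on which passage governs.

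**4. Comparison between arms**

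A nominal 12-week cut-off is the same in all three arms. Closure by transfer is not, because only community patients can transfer. Such a patient contributes the transfer itself as an SAE and may then contribute nothing further, while a hospital patient with the same clinical course stays under recording. These effects pull in opposite directions on the community count, so the net direction cannot be derived from the document.

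**5. Whether another passage closes the gap**

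- Follow-up to resolution applies to an SAE already recorded and does not detect a new one.
- The GP letter asks about surgery contacts and prescriptions during the trial period.
- Survival is monitored under standard practice (Non-participation in study), but nothing routes later deaths into the SAE count.

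**The case against.** The case for leaving the text alone has real force.

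- **The 28 days is a retrieval rule.** A reader might infer that deaths are followed for 28 days while other SAEs are not. The text asks only for autopsy data where they exist. That stands: it sets up no follow-up of deaths. It does create a class of deaths that the centre may know of and that the SAE rule excludes.
- **A fixed 12-week window is legitimate.** The trial compares venues rather than drugs, and a common window from randomisation is a sound basis. That stands too. A reader might infer that cutting off the tail biases the comparison, but a cut-off common to all arms does not do so by itself.
- **Early stoppers are kept to 12 weeks.** A reader might infer that they always lose the most coverage. Under Study duration they may lose none, as step 3 shows. The difficulty is that Study interventions, and the classing of transfer as withdrawal, point the other way.
- **Harm from the last cycle is not simply left out.** Events between the last dose and the final visit are recorded, and recorded SAEs are followed up. Continuing patients may attend a later visit that includes the AE diary. Only new events after the final visit are lost.
- **Tying the window to the last dose given could do harm.** Its length would then depend on a post-randomisation variable that venue may affect. It could also bring in venue switches after week 12, which count as SAEs and can arise only in the community arms. This objection stands and shapes the fix.
- **The article is condensed.** The full protocol may define the final visit. But the article itself states the end dates, and they do not agree.

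**Conclusion.** The concern holds as a problem of inconsistent windows and under-recording. SAE recording stops at a visit that may fall before week 12, against the 12-week retention in Study duration and the study-period count in Patient safety. Deaths and new serious events after that visit are outside the SAE count even when they fall within the document's own 28 days.

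The uncovered share of the 28 days is between 0 and 100%, on assumed gaps between last dose and visit. If an early final review closes recording, part of the 12-week period may be lost as well. Loss that differs between arms is possible through early withdrawal or transfer. Bias between arms is not shown, and neither its direction nor the number of events missed can be calculated from the document.

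**What to change.** Reconcile the passages with one rule.

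1. Set a single end date for SAEs and deaths, measured from a common origin and identical in all arms. An example is week 12 plus the document's own 28 days, which is 84 + 28 = 112 days. State the origin: data points are counted from the start of treatment, which may be up to 28 days after randomisation.
2. Apply it to every randomised patient, whether or not they stopped, transferred or had an early final visit.
3. Align the autopsy rule to the same date.
4. Keep the SAE count to week 12 as the main venue comparison and report the 28-day tail separately.
5. In that tail, do not count a switch of venue after week 12 as an SAE, since it can arise only in the community arms.

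A fixed end date is preferable to one that follows the last dose given, because the time at risk then does not depend on what happened after randomisation.

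Cost: a few sentences of protocol text, one hospital-record check or telephone call per patient, and SAE data that close about four weeks later. The change concerns recording and counting only, and patient management is unaffected.

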### Sample size

The EORTC QLQC30 questionnaire is a well validated instrument; this has been in widespread use since 1993 and is frequently used to assess quality of life of cancer patients in clinical trials. It comprises 30 questions representing various dimensions of quality of life. Of the 5 functional dimensions, emotional function might be considered to best reflect the levels of anxiety and satisfaction felt by patients taking part in this study. Using data on quality of life dimension mean scores determined by researchers interested in interpreting the results of the QLQC30 questionnaire, the standard deviation of the mean quality of life emotional function score for a large group of heterogeneous cancer patients is determined to be 24 [18,19].

With 130 patients randomised per arm, there is 80% power to detect a 10-point difference in mean QLQC30 score between any two study populations, at the 5% level of significance assuming a standard deviation 24. This allows for up to 30% of patients not providing information on the primary outcome, for reasons including withdrawal and non-completion of questionnaire. There is also 90% power to detect a 10-point difference between the home and GP surgery arms combined versus hospital using data from all three arms.

### Statistical Analysis

The primary analysis time-point is 12 weeks. The primary contrast is between home and GP surgery arms combined, versus hospital arm. Binary outcomes will be analysed using logistic regression. Continuous outcomes will be analysed using linear regression adjusting for randomisation stratifiers and the pre-randomisation baseline of the outcome in order to improve precision of the estimated intervention effects. Participants with valid data at follow-up but with missing data at baseline will be retained in the analysis by using the missing indicator method [20]. For measures repeated over time, linear mixed models will be used to analyse data from all time-points together, to assess for any patterns between study arms. The level of missing data will be compared by study arm. A logistic regression model will be used to examine whether baseline factors or intermediate study measures predict dropout by 12 weeks. With sufficient 12-week data, the impact of missing data on the main outcomes will be assessed using best and worst case sensitivity analyses, using multiple imputation [21], or otherwise using the linear mixed effects model with the available 4-week and 8-week data to model the 12-week effect from the trend in the outcome over time in each arm. Further analyses will include comparisons between pairs of arms, analyses at time-points and subgroup analyses, with subgroups defined by treatment intent and hospital.

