### Trial design and randomisation (Figure 1)

**Figure 1 F1:**
[figure not shown]
**Trial design**.

This is a prospective, randomised, controlled clinical trial conducted at two neighbouring Trusts in the Anglia Cancer Network: Addenbrooke's Hospital (CUH) and West Suffolk Hospital (WSH). Patients meeting the defined eligibility criteria are invited to take part in the study prior to or during their planned cancer treatment. All patients taking part provide written informed consent. Patients are randomised on a 1:1:1 basis to one of 3 arms: treatment delivered in the hospital out-patient and day unit environment (control arm A), treatment delivered at home (arm B) or treatment delivered in a GP surgery (arm C) using the method of minimisation with a random element to the assignment. Randomisation is performed centrally by statisticians located separately from trial recruitment and co-ordination and without knowledge of patients or their characteristics.

In the minimisation procedure the patients are stratified by centre (CUH or WSH), by treatment intent (cure, palliation in terms of disease control and life prolongation, or supportive care aimed at symptom control), ECOG performance status (PS 0, 1 or 2), gender, and prior cancer drug treatment (yes or no).

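### The primary week-12 regression leaves out patients without a 12-week score (up to 30% allowed for) and does not use their 4- and 8-week scores, so dropout that differs by arm can bias it; the already planned mixed model should be primary

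*Protocol article*

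**What the plan says.** All references are to the protocol article.

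- **Primary analysis (Statistical Analysis).** "The primary analysis time-point is 12 weeks". "The primary contrast is between home and GP surgery arms combined, versus hospital arm". The model is given as "Continuous outcomes will be analysed using linear regression adjusting for randomisation stratifiers and the pre-randomisation baseline of the outcome". Its only missing-data provision is for a missing baseline: patients who have a follow-up score are kept through a missing indicator. Nothing inside the model deals with a missing 12-week score.
- **Expected loss (Sample size).** "This allows for up to 30% of patients not providing information on the primary outcome".
- **Intermediate data (Recording and collection of data; Table 1).** The QLQ-C30 is completed at baseline and at 4, 8 and 12 weeks, and all four are mandatory collection points.
- **Other uses of those data (Statistical Analysis).** Linear mixed models on all time-points are planned without condition, to look for patterns between arms. Missingness is compared by arm, and a logistic model tests whether baseline or intermediate measures predict dropout.
- **Missing-data assessment (Statistical Analysis).** "With sufficient 12-week data, the impact of missing data on the main outcomes will be assessed using best and worst case sensitivity analyses", with multiple imputation named next. Otherwise the mixed model uses the 4- and 8-week data "to model the 12-week effect from the trend in the outcome over time in each arm". No threshold is given for sufficient.
- **Transfer and early stopping.** Recording and collection of data makes transfer from a community setting to hospital a withdrawal from the trial, and hospital-arm patients cannot transfer the other way. Study duration keeps patients who stop treatment early in the 12-week outcome collection.

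**The concern.** A patient with scores at 4 and 8 weeks but none at 12 contributes nothing to the primary estimate. Baseline adjustment protects that estimate only so far as dropout, given arm and baseline, is unrelated to how the patient has fared since.

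There is a reason in the design for dropout to differ by arm. Withdrawal by transfer to hospital can happen only in the two community arms. The triggers listed under Study interventions (toxicity, a serious adverse event, patient request, clinical judgement) could plausibly go with worse emotional function. If low-scoring community patients are lost more often, those who remain make community care look better. That is the direction of the trial's own hypothesis, so the error would be a false or inflated benefit.

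**Working it through.** **1. Reproduce the design figure.** Inputs from Sample size: difference 10, SD 24, 5% level (two-sided assumed), 30% missing.

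- The standard two-sample calculation at 80% power gives 91 evaluable patients per arm. 91 / 0.70 = 130, which matches "With 130 patients randomised per arm, there is 80% power to detect a 10-point difference in mean QLQC30 score".
- Allocation is equal ("Patients are randomised on a 1:1:1 basis to one of 3 arms"), so the primary contrast compares 182 observed community patients with 91 in hospital. Power is 80.3% for a pair of arms and 90.1% for the pooled contrast, matching the stated 80% and 90%.

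The sample size therefore already assumes analysis of the observed 70%: 273 of 390 patients.

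**2. Standard error of the primary contrast.**

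- Unadjusted: 24 × √(1/91 + 1/182) = 3.08.
- Adjusted for baseline, with an assumed correlation of 0.6: 3.08 × √(1 − 0.6²) = 3.08 × 0.8 = 2.46.

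**3. Bias by simulation.** The documents give no visit correlation, dropout mechanism or arm-specific loss, so these are assumptions. Overall missingness is about 30% throughout.

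*Large-sample simulation.* Log-odds of dropout rise by 1 per SD of lower score; correlation is 0.5 to 0.7, either constant or decaying with time; Monte Carlo error is about 0.1 point. Bias in points, positive favouring community care:

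| Dropout depends on | Missing, hospital / community | Week-12 regression | Using 4- and 8-week scores |
|---|---|---|---|
| Week-8 score | 30% / 30%, same mechanism | about 0 (−0.2 to +0.2) | about 0 |
| Week-8 score | 25% / 32.5% | +0.4 to +0.9 | about 0 |
| Week-8 score | 20% / 35% | +0.6 to +1.7 | about 0 |
| Unseen week-12 score | 30% / 30%, same mechanism | about 0 | about 0 |
| Unseen week-12 score | 20% / 35% | +2.0 to +2.7 (constant 0.5 or 0.6, decaying 0.7) | +1.6 to +1.9 (about +1.2 with constant 0.7) |

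*Trial-sized simulation.* 130 versus 260 patients, correlation 0.6, true effect 0, 600 trials per scenario:

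- Dropout driven by the last score in the community arms only: +1.80 for the regression, −0.05 for a likelihood model using all visits.
- Weaker dependence in the hospital arm as well: +1.29 and +0.04.
- The variance ratio favoured the all-visits model by 1.02 to 1.06.

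**4. Effect on type I error.** With z = bias / 2.46, the rejection rate under no effect is Φ(−1.96 + z) + Φ(−1.96 − z).

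- Bias 0.6: z = 0.24, rate 5.7%.
- Bias 0.8: z = 0.33, rate 6.2%.
- Bias 1.8: z = 0.73, rate 11.3%.

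**The case against.** The strongest reply is that this is a conventional, coherent plan: baseline-adjusted regression at the primary time-point, supported by a comparison of missingness, a dropout model, multiple imputation and a mixed model, with a sample size that fits it. Much of that stands, and it rules out several stronger readings.

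- *A reader might infer that the 4- and 8-week scores enter only through a fallback.* They do not. Mixed models on all time-points are unconditional, intermediate measures enter the dropout model, and they may enter the imputation, whose variables are not stated.
- *A reader might infer that the primary method is chosen after seeing the data.* The wording about sufficient 12-week data governs how the impact of missing data is assessed. The primary regression carries no condition. A threshold may also stand in an analysis plan that is not shown.
- *A reader might infer that the result is certain to be biased.* Bias was about 0 when dropout rate and mechanism were the same in each arm, and Study duration keeps early stoppers in follow-up.
- *A reader might infer that best and worst case limits would be uselessly wide.* That supposes every missing score is replaced by an extreme of the scale, which the text does not specify.
- *A reader might infer that a mixed model cures informative dropout.* It does not: where dropout depends on the unseen week-12 score, about 1.2 to 1.9 points remained.

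The reply leaves one thing unanswered. The primary estimate, on which the trial will be judged, is the one planned analysis at 12 weeks that ignores scores the trial has already collected. Supporting analyses do not change that.

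**Conclusion.** The point holds in a limited form. The primary estimate rests on observed 12-week scores, up to 30% may be missing, and the intermediate scores have only a descriptive or sensitivity role. If dropout depends on earlier scores and differs by arm in rate or mechanism, the estimate can be biased by roughly 0.6 to 1.8 points towards community care, with type I error of about 6% to 11%. Against a 10-point target this is modest, but it could turn a borderline result.

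The range describes the scenarios tried and is not a bound: a smaller gap in dropout between arms gave less, and equal dropout gave about 0. It depends on assumed correlations of 0.5 to 0.7 and assumed dropout mechanisms. The large-sample simulation also takes the 4- and 8-week scores as observed in patients who miss week 12, on which the documents give no figure.

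Whether transfer leads to a missing 12-week score is itself unclear, because Study duration and Recording and collection of data can be read differently. This is a change that should be made, not a fatal flaw.

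**What to change.** 1. Make the primary estimate the week-12 contrast, home and GP surgery combined versus hospital, from the mixed model already planned. Fit it to the 4-, 8- and 12-week emotional function scores with categorical time, arm × time, baseline × time, the minimisation factors and an unstructured covariance.
2. Keep the week-12 linear regression as a supporting analysis.
3. Replace the choice that turns on sufficient data, and the projection from a time trend, with multiple imputation under a stated range of score decrements applied by arm (for example 0 to 15 points), reporting where the conclusion changes. This is needed because the mixed model removes bias only under missing-at-random.
4. Reconcile Study duration with Recording and collection of data on whether patients transferred to hospital still give 12-week data.

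The cost is wording and a little programming; no new data are collected, and precision may improve slightly (variance ratio 1.02 to 1.06 in the simulation). The downside is that the main estimate then relies on missing-at-random given the observed scores, which step 3 tests.
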